#### Health care provider perspective

The analysis from the health care provider perspective will focus on analyzing the (work) processes of the new form of healthcare, especially the processes during an STH event, and will address issues relating (interdisciplinary) cooperation between stakeholders and the usability of the digital interactive health diary. Process mining techniques will be used to analyze the processes during an STH event as they take place. The results will be compared to the processes as they should be and will identify patterns, inefficiencies, and bottlenecks within the healthcare provider's operations [35]. Descriptive methods will be used to analyze the data collected on (interdisciplinary) collaboration and usability.

There will be an internal interim evaluation from all the three perspectives after half of the intervention time passes. The results will be shared with the participating institutions.

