###  Participants

 Assuming that the hospitalization rate in the patient group before the intervention is approximately 20 percent [2] with a potential of reduction to 15 percent during intervention (a reduction of 25 percent), with a power of 90 percent and a significance level of 0.05, the calculated sample size is 1,210 patients for the intervention group [18]. To address sample attrition due to heightened mortality in the research group as well as other unforeseeable drop-outs, about 25 percent additional patients should be recruited, resulting in a total sample size of *n* = 1,500 participants in the intervention group, with at least the same number of controls to be drawn. GPs will be recruited through outreach by the KV, which in turn will recruit eligible participants for the study. Alternatively, the participants will be recruited by a study physician to relieve the GPs. The informed consent will be obtained from the participants by either their GP or the study physician. The intervention group will be derived from eligible insurees of the participating health insurance companies, who are 60 years or older, reside in Berlin in their own home, receive support from a caregiver, and have been either officially granted “care level” 1 or higher, have applied for it or been assessed by their GP as needing “care level” 1 or higher. In Germany, five “care levels” represent a scale used to classify the level of care needed by individuals requiring long-term care. The respective care level determines the subsidies those individuals receive through their nursing care insurance provider. Participants can withdraw their consent to participate in the study anytime. If participants stop meeting the inclusion criteria listed above at some point, e.g. leave their participating insurance company, they will be excluded from the study.

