###  Study period

The study period is designed to take place within eight quarters (24 months). During the first six quarters (18 months), the intervention group will be gradually recruited for the new form of healthcare, so that individuals who are added at the end of the recruitment period can utilize the new form of healthcare for at least two quarters (6 months). For the control group 1 and the operationalization of control variables, the claims data of the health insurance companies from a pre-observation period of eight quarters before entry into the new form of healthcare will be used. The surveys on the secondary endpoints take place at the beginning of the intervention (weeks 2-4) and after 3 to 6 months during the intervention. The control group 2 is surveyed at a congruent time interval. Figure 2 illustrates the planned data collection period and the cumulatively increasing sample size of the intervention group.

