###  Outcomes

Within the evaluation, three perspectives will be considered: health insurance, patients, and health care providers. All outcome variables are shown in Table 1.

**Table 1 Tab1:** Outcomes

**Outcome**	**Operationalization**	**Data source**	**Outcome type**

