#### Health insurance perspective

On the level of the health insurance, utilization and total costs will be compared between intervention group and control group 1. Concerning utilization, number of hospital stays, days spent in inpatient hospital care, and number of emergency situations will be analyzed. For these measures, a second analysis will focus on ambulatory-care sensitive hospital stays and emergency responses [13, 19]. Furthermore, the volume of healthcare provided by the outpatient sector will be evaluated. For the economic evaluation, the total costs of the new form of healthcare in addition to costs for standard care within the intervention group will be assessed and compared to the costs of standard care for the control group 1 [20–22].

The rationale for selecting the number of treatments (e.g. hospital stays) and the overall treatment costs as the primary outcome domains is based on their direct relevance to the study’s objectives and clinical impact. The number of treatments provides a quantifiable measure of intervention utilization, offering insights into the intensity and frequency of care required. Meanwhile, total treatment costs are essential for evaluating the economic implications of the intervention, which is particularly important for healthcare systems focusing on cost-effectiveness and resource allocation. Together, these domains allow for assessing both the practical and financial viability of the intervention, making them highly pertinent to stakeholders and policymakers.

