## Trial status

Start of recruitment was March 25, 2024, and will continue until June 30, 2025. The observation period will end on December 31, 2025. By the time of submission (November 17, 2024), *n*= 36 participants have already been enrolled in the trial. The results will be reported to the funder, as well as shared with the scientific community and the public in a publication.

Authorship eligibility guidelines within the study consortium are established to ensure that all contributors who meet the criteria for authorship are appropriately credited in publications. Principles of intellectual contribution and accountability in the authorship process are prioritized. There are no intended uses of professional writers for the preparation of manuscripts; instead, all publications will be collaboratively developed by the research team members.

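### Half-time results from all three perspectives go to the participating institutions with no limit on content, on the natural reading including the comparative primary outcomes, before observation ends

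*Protocol article*

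**What the plan says.** The rule is in the last paragraph of Analysis, Health care provider perspective: "There will be an internal interim evaluation from all the three perspectives after half of the intervention time passes". The next sentence reads: "The results will be shared with the participating institutions". Nothing there restricts which results are shared, says when they are released or defines the institutions.

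Other sections supply the content:

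- Outcomes names the perspectives: "three perspectives will be considered: health insurance, patients, and health care providers".
- Outcomes, Health insurance perspective, says that "utilization and total costs will be compared between intervention group and control group 1". Its second paragraph confirms that these are the primary domains: "The rationale for selecting the number of treatments (e.g. hospital stays) and the overall treatment costs as the primary outcome domains". Table 1 likewise marks hospital stays, emergency responses and costs as primary.
- Participants describes recruitment: "GPs will be recruited through outreach by the KV, which in turn will recruit eligible participants". A GP or a study physician takes consent.
- Intervention places the on-call service and the consulting physician at the KV. The consulting physician decides on further care in an STH event, and the options include emergency use and hospital referral. The telemedical assistance sits at the university hospital.
- Trial status gives the dates: "Start of recruitment was March 25, 2024, and will continue until June 30, 2025". Observation ends on 31 December 2025.

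**The concern.** The study is open and non-randomized, and the network partners who would receive the results can influence both who enters and what is counted. The KV does the outreach to recruiting GPs. Its consulting physician takes referral decisions that feed directly into hospital stays and emergency responses. If these partners learn an early effect estimate, enrolment may become more or less selective and the readiness to refer may shift. The direction cannot be predicted.

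Control group 1 is drawn from claims data and is not part of the network, so a reaction would fall on the intervention group alone and would be read as an effect of the intervention. The Participants section claims that observed effects can be attributed specifically to the intervention, and this release works against that claim. The Limitations section does not mention it.

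**Working it through.** **1. What the interim covers.** All three perspectives are included. The health insurance perspective is defined as the comparison with control group 1, and no part of it is excepted. As written, the comparative primary outcomes are inside the shared results. This is inferred from the definitions; no sentence says it outright.

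**2. When half-time falls.** Inputs are from Trial status: start 25 March 2024, recruitment closes 30 June 2025, observation ends 31 December 2025. Months are days / 30.44.

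| Reading of half-time | Date | Recruitment left | Observation left |
|---|---|---|---|
| Midpoint of the stated dates (646 / 2 = 323 days) | 11 Feb 2025 | 139 days = 4.6 months | 323 days = 10.6 months |
| Month 12 of 24 | 25 Mar 2025 | 97 days = 3.2 months | 281 days = 9.2 months |

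These figures assume release on the half-time day, so they are upper bounds. If analysis and reporting used up the whole recruitment window, 323 − 139 = 184 days (6.0 months) of observation would still follow. The Study period section on its own (18 months of recruitment within 24) would leave 6 and 12 months at month 12; the stated calendar is shorter.

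**3. How much of the data comes after half-time.** Assume uniform accrual over R, study length E, interim at T and no attrition. The share of intervention person-time accrued by T is (T²/2) / (R·E − R²/2).

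- Planned schedule: 72 / (432 − 162) = 72 / 270 = 27%.
- Stated dates, midpoint: 52,164.5 / (298,452 − 106,722) = 52,164.5 / 191,730 = 27%.

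So about 73% of person-time would come after half-time. Actual accrual was slower at first: 36 of 1,500 (2.4%) by 17 November 2024, after 237 of 462 recruitment days (51%). The later share is therefore probably larger.

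**4. How precise an interim estimate would be.** The planning rates of 20% and 15% are the right inputs, since they reproduce the plan's sample size. With two-sided 0.05 and 90% power, (1.960 + 1.282)² × (0.20 × 0.80 + 0.15 × 0.85) / 0.05² gives 1,209, and the pooled-variance form gives 1,212, against the stated 1,210.

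The 95% half-width for the difference, with equal groups, is 1.96 × √(0.2875 / n):

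- n = 49 (constant pace, 36 / 237 × 323): ±15.0 points.
- n = 750 (half of 1,500, for illustration): ±3.8 points.
- n = 1,000 (uniform accrual at month 12, 12/18 × 1,500): ±3.3 points.

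The planned difference is 5 points. These widths give full planning rates to people with only partial follow-up and ignore 1:n matching, so they are rough. They show how noisy an early estimate would be if accrual stays slow. They do not measure bias.

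**5. What matching can repair.** The propensity score uses demographics, care level, region, morbidity and utilization from before the study. A shift in the mix of people enrolled would be partly absorbed. A change in referral behaviour happens after entry and is not touched.

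**6. Whether anything in the plan needs the release.** Outcomes, Health care provider perspective, already provides formative feedback: process mining every three months and later monthly, three-monthly stakeholder questions, and ratings after each event, so that weaknesses can be corrected promptly. None of this uses effect estimates, and the article attaches no decision to them.

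**The case against.** The strongest reply is that much of this is inferred. The interim paragraph names no effect estimate, no test and no comparison with control group 1. The health insurance perspective also holds non-comparative content, such as the cost of the new form of care, and the matched comparison needs linked claims data that may not be ready at half-time. The article mostly uses the word participating for health insurance companies. Only the date of the evaluation is fixed, not the date of release. The on-call route applies only when the GP is unreachable, and initial triage uses a structured instrument. In a pragmatic complex-intervention study, mid-course feedback is intended. Access limits may also be set out in a full protocol that is not shown.

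Most of this stands as a limit on certainty, and it is why the windows are given as upper bounds. It does not remove the point, because the article states scope, timing and sharing as a rule and exempts nothing. The Data sources section does restrict each evaluation party to the data it needs, but that governs access to data, not who receives results. The intended feedback concerns processes and providers.

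Four stronger readings are tempting but not supported:

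- That the article expressly releases comparative effects to recruiters during recruitment. Content, recipients and release date are natural readings, not explicit text.
- That participants' questionnaire answers will be distorted. Participants are not institutions, and no route to them is stated.
- That this is a formal interim test that inflates the type I error. No test, stopping rule or interim claim of effect is stated.
- That the wide intervals show the size of the bias. Imprecision and operational bias are different things.

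**Conclusion.** The point holds as a weakness in a stated design choice. It should be changed, but it does not invalidate the study. Half-time precedes the close of recruitment by up to about 3 to 5 months and the end of observation by up to about 9 to 11 months. Under uniform accrual some 73% of intervention person-time lies after it. The route to bias is credible, because one network partner both does the recruitment outreach and triages events, and because only the intervention group could react. How large the bias would be cannot be computed from the document.

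The conclusion rests on three assumptions: that all three perspectives means what the Outcomes section says, that the participating institutions include network partners such as the KV, and that release follows half-time without a long delay. If the release were late, the recruitment concern would fade, but the referral concern would remain for as long as observation continues.

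**What to change.** Replace the sharing sentence with one that limits content. At half-time the participating institutions receive process-mining, cooperation and usability findings plus recruitment and data-quality counts. Comparative utilization, cost and patient-reported results stay with the evaluators, or are not computed, until observation ends on 31 December 2025 and the data are locked. The sentence should also say which institutions are meant.

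If results have already been shared, record what went to whom and on what date, and compare enrolment mix and the proportion of STH events referred to hospital before and after that date.

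The cost is one sentence in the protocol and a longer wait for outcome results at the partner institutions. Formative feedback and the sample size are unaffected.

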##  Discussion

Demographic change leads to a larger population of older individuals and consequently more people facing mobility issues and care dependency. Furthermore, the shortage of nursing staff and other medical personnel will exacerbate the situation [40]. New forms of care are needed to facilitate the work of healthcare providers and improve the health of care recipients. Advances in medicine and technology can help maintain or even improve the quality of life among the growing older people population [41]. With Stay@Home – Treat@Home, care dependent individuals can be monitored for health at home and provided medical services. Supported by a closely coordinated care network spanning both outpatient and inpatient sectors, and leveraging state-of-the-art technologies and telemedicine, the aim of the study is to evaluate whether this approach leads to a reduction in hospital admissions [42] and alleviate the burden on the healthcare system [43].

The digital interactive health diary serves various functions. Firstly, it facilitates direct communication among patients, their caregivers, and healthcare providers. Regular entries related to health queries and measurements are guided and monitored by the GP. The GPs can access the health documentation stored by patients and caregivers at any time, allowing to remotely monitor the patient's condition. Secondly, patients and their caregivers can more easily detect any changes in health status themselves and take appropriate measures [44]. Thirdly, should an intervention be necessary at the patient's home, personnel of nursing aid services as well as physicians can also access the entries to gain an understanding of the patient's health trajectory. They can document the measures they have taken, thereby providing a record of the course of events for all other healthcare providers involved.

If the digital interactive health diary is to be included in regular standard care, it should not only be beneficial for the patients’ health and cost effective for health insurances. It also has to meet the needs of its direct users. In Germany, the documentation burden for healthcare providers is quite high [45]. This is why this evaluation study considers not only the perspective of the patients and the health insurance, but also evaluates the experiences of the healthcare providers using this new digital interactive health diary [46]. This way, Stay@Home – Treat@Home could potentially take a significant step forward in the advancement of medical and nursing care.

###  Limitations

The approach to recruitment or data access for the intervention and control group 1, respectively, will be different, which can cause different selection bias in the intervention and control group 1.

A further aspect of the study, which contributes to the selection bias is, e.g. the fact that the study will only be conducted in Berlin. Therefore, regional differences cannot be considered and the generalization of the results to rural areas must be approached with caution. Only participants with a caregiver or members of participating health insurance companies can be included in the study, which may also lead to a certain selection bias. However, part of the bias is taken into account by including persons who are insured with a health insurance company that is not participating in the project in control group 2 with regard to the survey on the secondary endpoints. Additionally, for ethical and practicality reasons, a randomized controlled trial cannot be implemented.

There is also a possibility of a measurement bias, if the billing data is not maintained carefully by the responsible organizations. A response bias is possible in the data coming from the digital interactive health diary.

###  Strengths

The strengths of the study include its high ecological validity, as this study is conducted under real world conditions within the frame of real healthcare services in Germany.

## Trial status

Start of recruitment was March 25, 2024, and will continue until June 30, 2025. The observation period will end on December 31, 2025. By the time of submission (November 17, 2024), *n*= 36 participants have already been enrolled in the trial. The results will be reported to the funder, as well as shared with the scientific community and the public in a publication.

Authorship eligibility guidelines within the study consortium are established to ensure that all contributors who meet the criteria for authorship are appropriately credited in publications. Principles of intellectual contribution and accountability in the authorship process are prioritized. There are no intended uses of professional writers for the preparation of manuscripts; instead, all publications will be collaboratively developed by the research team members.

## Data Availability

No datasets were generated or analysed during the current study.

## Abbreviations

BGW: German Social Accident Insurance Institution for the Health and Welfare services
G-BA: German Federal Joint Committee
GP: General practitioner
KV: Association of Statutory Health Insurance Physicians
OSSS-3: Oslo social support scale
SmED: Structured Initial Medical Assessment in Germany
STH: Stay@Home – Treat@Home
QoL-AD: Quality of Life-Alzheimer’s Disease
UCLA-LS: University of California Los Angeles-Loneliness Scale
WHO-5: Wellbeing measures in primary health care
